### Secondary outcomes:

Secondary outcomes will include the following:

- Mean proportion of adequate reporting of the 10 most important and poorly reported CONSORT items, considering each sub-item (see also “Assessment of outcomes”) as a separate item.
- Mean proportion for each of the 10 most important and poorly reported CONSORT items separately (including also separate analysis of sub-items).
- Time from assigning an academic editor until the first decision (as communicated to the author after the first round of peer-review).
- Proportion of articles directly rejected after the first round of peer-review.
- Proportion of articles published.

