### Data collection methods:

The outcomes will be assessed independently by two (blinded or at least partially blinded; see “blinding”) outcome assessors with expertise in the design and reporting of clinical trials. Any disagreement will be resolved by consensus or if necessary by consulting a third assessor. To ensure consistency between reviewers, we will first pilot the data extraction form; any disparities in the interpretation will be discussed and the data extraction form will be modified accordingly.

Adequate reporting of items will be assessed from published full-text publications adhering to the CONSORT C-short checklist (21). The following included items have sub-items which will be extracted separately:

- Outcomes (item 6a): (i) Define primary outcome, (ii) how it was measured, (iii) at what time point, and (iv) the analysis metric (e.g. change from baseline, final value).
- Sample size (item 7a): (i) The estimated outcomes in each group, (ii) the  $\alpha$  (type I) error level, (iii) the statistical power (or the  $\beta$  (type II) error level), (iv) for continuous outcomes, the standard deviation of the measurements
- Blinding (item 11a): Is the blinding status clear for the following persons: (i) Healthcare provider, (ii) patients, and (iii) outcome assessors.
- Funding (item 25): (i) The funding source, and (ii) the role of funder in the design, conduct, analysis, and reporting.

All items will be judged as either “yes” meaning adequately reported, “no” meaning not adequately reported, or “NA” meaning that this sub-item is not applicable for this RCT. Items with different sub-items will only be judged as adequately reported if all relevant sub-items were adequately reported.

- Time from assigning an academic editor until the first decision: The day when the academic editor was assigned and the day of the first decision (e.g. major revision, minor revision, rejected) will be extracted to calculate the number of days until the first decision.
- Proportion of articles directly rejected after the first round of peer-review: Articles which were not invited for re-submission will be labelled and counted.
- Proportion of articles published: Articles which will be published will be counted and collected for data extraction.

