#### 4.6. Sample size

For the sample size calculation we hypothesise in a first scenario (Table 3) that the intervention C-Short will result in a 25% relative increase in adequate reporting compared to the control (meaning that 70% of items will be adequately reported in the intervention group and 56% in the control group). This is based on the rate of reporting of the 10 most important and poorly reported items was 0.56 (meaning that a mean of 56% of the 10 most important and poorly reported items were reported) in the control group of a previous study called WebCONSORT (38). The standard deviation (SD) in the same study was 0.23. However, we calculated our sample size to account for a slightly bigger variability in our data ( $SD = 0.25$ ). To demonstrate a significant difference with a power of 90% and a type 1 error at 5% a total of 136 articles will be required in this scenario (68 per treatment arm; based on a two sided t-test).

The staff from one journal which will most likely be included (i.e. *PLoS One*) pointed out that 3 out of the 10 assessed items (i.e. item “Registration”, “Protocol”, and “Funding”) should always be implemented given their template. Assuming that this journal will recruit a high proportion, and that also other journals might update their templates, we increased the sample size in a second scenario, in which all these 3 items would have an overall adherence of 90% in the control arm (Table 3). This would entail an overall baseline adherence with the 10 CONSORT-short items of 71%. Based on a two sided t-test, a sample size of 166 (83 per treatment arm) will have a power of 80% to find a 15% relative increase (71% adherence in control group; 82% adherence in intervention group;  $SD = 0.25$ ; a type 1 error at 5%).

Since the final sample size will be based on the number of articles published, rather than on the number of manuscripts randomised, eligible RCTs will be included and randomised until the number of 83 published RCTs is reached in each arm (resulting in no less than 166 articles), to avoid loss of power due to potential imbalance between arms. Recruitment will be stopped as soon as both arms reach the sample size of 83. After recruitment stop we will wait three month so that manuscripts which are still in production can be published. Manuscripts which are published after the three month period will be excluded.

**Table 3:** Assumptions for sample size calculations in two different scenarios.

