## 4.8 Statistical methods

### 4.8.1 Populations of analysis

The main population for analysis will be all manuscripts randomised and accepted for publication in the participating journals. Differently from RCTs conducted with patients, where drop outs need to be carefully considered (e.g. multiple imputation of missing data), we are only interested in the reporting adherence of RCTs that are published. All outcomes will be calculated based on the main population for analysis. The secondary outcome "Time to the first decision", will additionally be calculated considering all randomised manuscripts (including the ones which were not published).

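### Section 4.8.1 confines all outcomes to accepted manuscripts, so the rejection and publication outcomes have essentially nothing to compare between arms

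*Protocol*

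**What the plan says.** Section 4.8.1 sets the population: "The main population for analysis will be all manuscripts randomised and accepted for publication in the participating journals". It then applies that population without restriction: "All outcomes will be calculated based on the main population for analysis". One outcome, time to first decision, gets a second analysis; it "will additionally be calculated considering all randomised manuscripts (including the ones which were not published").

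Section 4.4 lists five secondary outcomes. Two of them are "Proportion of articles directly rejected after the first round of peer-review" and "Proportion of articles published". Under data collection methods in the same section, the first is put into practice as "Articles which were not invited for re-submission will be labelled and counted" and the second as "Articles which will be published will be counted and collected for data extraction". Both are to be taken from the journals' editorial software. Table 2 in section 4.5 places the rejection outcome at the journal's first decision, a separate time point from publication.

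Section 4.8.4 plans between-arm differences with 95% confidence intervals and a 0.05 threshold for the secondary outcomes. Section 4.6 recruits until each arm has 83 published articles, waits three months, and then adds: "Manuscripts which are published after the three month period will be excluded".

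**The concern.** A rejection rate needs rejected manuscripts in its denominator, and a publication rate needs unpublished ones. Section 4.8.1 takes both out before either outcome is calculated. Since the authors wrote an explicit addition for one editorial outcome and named only that one, the text cannot be read as quietly covering the other two.

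The primary outcome is measured only in accepted manuscripts, a set formed after randomisation. The intervention asks reviewers to look harder at reporting, so it could plausibly change which manuscripts are accepted. Of the listed outcomes, rejection and publication by arm in all randomised manuscripts would show such selection most directly. The stopping rule adds to their importance. Recruiting until each arm has 83 published articles pushes the published counts towards equality, so a difference in acceptance would show mainly in the numbers randomised.

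**Working it through.** The protocol gives no expected value for either proportion, so there is no figure of its own to reproduce on this point. The sample size is used here only as the size of the analysed set. It does reproduce: a two-sided t-test with difference 0.82 − 0.71 = 0.11, SD 0.25, alpha 5% and power 80% gives 82.05, rounded up to 83 per arm.

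**Step 1. Proportion directly rejected, on the stated population.** Section 4.4 defines direct rejection as no invitation to re-submit. Such a manuscript is not accepted, so it is not in the main population. P(rejected | accepted) = 0 in each arm. At target size: 0/83 v 0/83.

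**Step 2. Proportion published, on the stated population.** The population is defined by acceptance and the outcome by publication, so the two are not identical. Manuscripts published after the three-month wait are excluded under section 4.6; they do not stay in as unpublished. What remains is an accepted manuscript that never appears in print. Without any such case the result is 83/83 v 83/83. As an illustration (an assumption), one such case in one arm gives 83/84 = 98.8% v 100%, and that would reflect a production event after acceptance, not an editorial decision.

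**Step 3. Planned inference.** For each outcome the difference is 0 and the standard error is √[p(1−p)/83 + p(1−p)/83] with p = 0 or p = 1, which is 0. The confidence interval has no width and the test is undefined, whatever the intervention does.

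**Step 4. The same outcome in all randomised manuscripts.** The protocol states no publication rate, so a range is assumed, equal in both arms. Randomised per arm: n = 83/p, rounded up. Approximate 95% half-width for the difference in proportion published: 1.96 × √[2p(1−p)/n]. Example at p = 0.5: n = 166, and 1.96 × √(0.5/166) = 0.108.

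| Assumed publication rate | Randomised per arm | Half-width (percentage points) |
|---|---|---|
| 30% | 277 | 7.6 |
| 40% | 208 | 9.4 |
| 50% | 166 | 10.8 |
| 60% | 139 | 11.5 |
| 70% | 119 | 11.6 |

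The formula treats n as fixed, although recruitment stops on the published count, so these widths are a guide only. They show that the corrected outcome carries some information, where the stated one carries essentially none.

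**The case against.** The best reply is that an all-randomised denominator was plainly meant. Articles not invited for re-submission can be counted only outside the accepted set. Table 2 puts rejection at the first decision. Both proportions come from the editorial software, and section 4.7 on data management lists the final decision among the extracted fields. The reason section 4.8.1 gives for the restriction, an interest in the reporting of published trials, fits only the CONSORT item outcomes. All of this stands as evidence of intent. It does not remove the problem, because no sentence gives the two proportions that denominator, and section 4.8.3 repeats that only accepted manuscripts are included. Nor is this a detail left to a later analysis plan: the protocol fixes the population, and fixes it in conflict with its own outcomes.

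Some stronger readings are not supported:

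- A reader might infer that the results would be taken as false evidence of no effect. Figures of 0% v 0% and about 100% v 100% are visibly degenerate, and an analyst would notice. The realistic risk is that the denominator is then chosen after the data are seen.
- A reader might infer that these outcomes are the trial's only check on harsher reviewing. The protocol does not give them that purpose. Time to first decision is already analysed in all randomised manuscripts, and reviewer comments are to be examined where available. Neither measures rejection directly.
- A reader might infer that exactly 100% published follows by definition. Only the 0% rejected does.

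**Conclusion.** The point holds as a contradiction within the protocol. As written, two of the five listed secondary outcomes cannot show a difference of any use: rejection is 0% in both arms by definition and publication is essentially 100% in both. This rests on reading section 4.8.1 literally, and on an article that was not invited for re-submission not being accepted as the same submission.

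The reach is limited. The records needed for a meaningful analysis are already due to be extracted, so the information is not lost. The sample size is unaffected, and the calculation of the primary outcome does not change. What is missing is a prespecified way to see whether acceptance differed by arm, which matters for interpreting a primary comparison made only among accepted manuscripts. A reader might also infer that time to first decision needs a new main analysis. It does not: section 4.8.1 already provides the all-randomised version, and its rank is a matter of preference.

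**What to change.** In section 4.8.1, limit the sentence that assigns every outcome to the main population so that it covers the CONSORT item and sub-item outcomes only. Add that the proportion directly rejected after the first round and the proportion published are analysed in all randomised manuscripts by allocated arm. Time to first decision can stay as it is.

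The new denominator needs a rule for unresolved manuscripts, because recruitment stops once both arms reach 83 published articles and some randomised manuscripts may then have no outcome. State how those still undecided, in production, or published after the three-month cut-off are classified. One option is to count them as not published by the cut-off and report their number by arm. State likewise how a manuscript with no first decision by then enters the rejection outcome.

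The cost is a paragraph of text before analysis. The small downside is that some manuscripts will have an incomplete outcome at the cut-off. Sections 4.2 and 4.3 foresee restricted system access at some journals, so it is worth confirming that final decisions can be obtained there for every randomised manuscript.

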#### 4.8.2 Data analysis

All quantitative variables will be described using means and standard deviations, or median and interquartile ranges in case severe departures from a normal distribution are identified. Data distribution will be inspected visually (i.e. by histograms) instead of performing formal statistical tests for normality. Categorical variables will be described using frequencies and percentages. For the primary and secondary outcomes, we will estimate the difference between means between the two groups and report them with respective 95% confidence intervals.

#### 4.8.3 Analysis of primary endpoint

The primary outcome will be the difference of the mean proportion of adequately reported items of the 10 most important and poorly reported CONSORT items. If the data on the primary outcome is normally distributed then the two groups (i.e. C-short plus usual practice vs. usual practice) will be compared using an unpaired Student's t-test to compare the unadjusted mean proportion of adequate reporting. If the data is not normally distributed, comparisons will be performed using a non-parametric equivalent test (i.e. Wilcoxon-Mann-Whitney test for testing whether the population medians of the two groups are the same).

For the analyses of the primary outcomes a p-value of 0.05 (5% significance level) will be used to indicate statistical significance and treatment effect (mean difference) reported with 95% confidence intervals (or median and respective interquartile ranges, in case of asymmetric distribution). Exact p-values will be presented up to three decimal places. We anticipate there will be no missing data in this study, neither at the individual C-short items, nor at the manuscript level. This is due to the study design, which will include only the randomised manuscripts that are accepted for publication.

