#### 4.7 Randomisation and blinding

Articles, which meet the eligibility criteria as a primary report of an RCT, for which the journal decides to send out for external peer review will be randomised into one of the two groups (allocation 1:1). The randomisation list will be created by the study-randomizer system (43) using random block sizes between 2 and 8 and stratification by journal. As soon as the first peer-reviewer accepts the invitation, the manuscript will be included and randomised to one of the two intervention arms. One of the investigators (BS) will log onto the study randomizer-system (43) entering the study identification number (ID; provided from the Journal), the study title, as well as the journal the study was submitted to. Subsequently, all additional peer-reviewers accepting the invitation to review the same manuscript will receive the same intervention (C-short plus usual practice or usual practice only) as the first peer-reviewer.

Authors will be blinded to the intervention allocation. Editors will not be actively informed about the randomisation (possible exception listed under “4.3 Interventions”). To avoid potential bias, peer reviewers and manuscript authors will not be informed of the study hypothesis, design and intervention.

Outcomes will be assessed in duplicate (see assessment of outcomes). At least one outcome assessors will be blinded. Due to restricted resources it might be possible that the investigator conducting the randomisation (BS) will be included in the data-extraction from published manuscripts.

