#### 4.8.5 Pre-specified subgroup analysis

No formal subgroup comparative analysis is planned for the primary or secondary outcomes. However, the effect of the intervention on the primary outcome within subgroups, will be presented using forest plots to visually examine whether it differs according to some variables, such as: (1) Journals that actively implement the CONSORT Statement (defined as requiring authors to submit a completed CONSORT checklist alongside their manuscript) vs. journals that are not actively implementing the CONSORT Statement; (2) sample size ( $n < 100$  vs.  $n \geq 100$ ); and (3) impact factor ( $<5$ ,  $5.1-10$ ;  $>10$ ) as there is evidence that higher impact factor as well as higher sample size are associated with higher adherence to reporting guidelines (44). These analyses will be exploratory, with the aim of supporting new hypothesis generation, rather than conclusive.

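### The primary comparison makes no use of RCT sample size, which the protocol calls prognostic and already extracts, or of journal, the stratification factor: an avoidable but probably modest loss of precision

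*Protocol*

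**What the plan says.** Section 4.8.3 compares the arms by an unpaired "t-test to compare the unadjusted mean proportion of adequate reporting". It then adds: "If the data is not normally distributed, comparisons will be performed using a non-parametric equivalent test", namely Wilcoxon-Mann-Whitney. The result is to be given as a "treatment effect (mean difference) reported with 95% confidence intervals", or as medians with interquartile ranges if the distribution is asymmetric. No covariate enters either branch, and the protocol describes no adjusted analysis of the primary outcome anywhere.

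Section 4.8.5 states that "there is evidence that higher impact factor as well as higher sample size are associated with higher adherence to reporting guidelines". The RCT's sample size, cut at 100, and the journal's impact factor are used there only to draw exploratory forest plots; the section opens with "No formal subgroup comparative analysis is planned for the primary or secondary outcomes".

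Table 2 (section 4.5) lists sample size among the trial characteristics to be extracted from published manuscripts. Under Randomisation and blinding, the allocation list is made "using random block sizes between 2 and 8 and stratification by journal". The primary test does not carry that stratification forward.

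**The concern.** The protocol names a predictor of its own outcome, plans to collect it for every article analysed, and leaves it out of the one comparison where it could help. Variation in the score that RCT size could explain stays in the residual variance and widens the interval. The same holds for journal: if adherence differs between journals, balancing allocation by journal removes that variation from the estimate, but an unadjusted standard error still counts it.

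RCT size is a legitimate covariate although it is read from the published article. The number randomised was settled when the reported trial was conducted, before its manuscript reached peer review, and a checklist sent to reviewers cannot change it.

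What is at stake is the width of the primary interval and a few points of power in a trial planned at 80%. The adjustment has to be written down in advance; adopted after the data are seen, it would carry little weight.

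**Working it through.** **Inputs from the protocol (section 4.6, second scenario, which sets the final size).** Control 71%, intervention 82%, so a difference of 0.11; SD 0.25; two-sided t-test with "a type 1 error at 5"%; 83 articles per arm; stated power 80%.

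**Input not in the protocol.** The correlation r between log RCT size and the score. Section 4.8.5 asserts an association without a figure, so r is assumed and varied from 0 to 0.4.

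**Step 1: the plan's own figure.** The standardised difference is 0.11 / 0.25 = 0.44. The noncentral t gives 82.05 per arm for 80% power, rounded up to 83. Power at 83 per arm is 80.5%. The first scenario (0.70 against 0.56, SD 0.25, power 90%) gives 68 per arm, as stated. Both figures reproduce.

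**Step 2: the unadjusted interval.** Half-width = t(0.975; 164 df) × SD × √(2/n) = 1.9745 × 0.25 × √(2/83) = 0.0766, or 7.7 points.

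**Step 3: adjust for log RCT size.** The residual SD becomes 0.25 × √(1 − r²). The half-width uses 163 df and a small-sample factor of √(1 + 1/(2n − 4)) = √(1 + 1/162) = 1.0031 for one covariate. Example, r = 0.3: residual SD = 0.25 × 0.954 = 0.2385; half-width = 1.9746 × 0.2385 × √(2/83) × 1.0031 = 0.0733; ratio 0.0733 / 0.0766 = 0.957.

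Power is from the noncentral t with standardised difference 0.44 / √(1 − r²) and 83 per arm.

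| Assumed r | r² | Half-width | Change in CI width | Power for 11 points |
|---|---|---|---|---|
| 0 | 0 | 0.0769 | 0.3% wider | 80% |
| 0.1 | 0.01 | 0.0765 | 0.2% narrower | 81% |
| 0.2 | 0.04 | 0.0753 | 2% narrower | 82% |
| 0.3 | 0.09 | 0.0733 | 4% narrower | 84% |
| 0.4 | 0.16 | 0.0704 | 8% narrower | 87% |

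Break-even, where the gain just pays for the lost degree of freedom, is at r² of about 0.006.

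**Step 4: what r means on the protocol's own cut.** If half the articles report RCTs of at least 100 participants and the two halves differ by D in mean score, then r² = (D/2)² / 0.25². A 10-point gap gives 0.05² / 0.25² = 0.04, so r = 0.2. A 15-point gap gives 0.075² / 0.25² = 0.09, so r = 0.3. A 20-point gap gives 0.10² / 0.25² = 0.16, so r = 0.4. The half-and-half split and the gaps are assumptions.

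**Not computed.** The effect of adding journal. The protocol gives neither the number of journals nor the variation in adherence between them.

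**The case against.** The strongest reply is that nothing here is wrong. The unadjusted t-test is valid, it matches the test used for the sample size, and the stated size reproduces. All of that stands, and it limits the point to efficiency.

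The gain is also uncertain. No value of r can be taken from the documents, and at r = 0.1 or below adjustment buys practically nothing. A reader might infer that the planned interval is certainly wider than it need be; the documents support this only if the cited association holds, with some strength, for this ten-item score.

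A reader might also infer a second harm, that chance imbalance in RCT size biases the result. With half the RCTs at or above 100, the between-arm difference in that share has SD √(2 × 0.25 / 83) = 7.8 points. With an assumed 15-point gap, a 2-SD imbalance moves the estimate by 2 × 0.078 × 15 = 2.3 points. But that is the r = 0.3 row of the table seen another way: the unadjusted standard error already allows for it.

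Nor is 80% power the whole picture. Section 4.6 raised the SD from 0.23 to 0.25 and took the more cautious scenario. At SD 0.23 the power of 83 per arm for 11 points is about 86%, and under the first scenario's 14 points it is about 95%.

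Finally, it is tempting to say that RCT size varies widely within journals, so that journal cannot stand in for it. The protocol gives no distribution of RCT size, and the point does not need that claim.

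What survives is the trade: about 0.3% of interval width at risk from the size covariate, against a possible gain of several per cent, from a variable already being extracted.

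**Conclusion.** The point holds as a cheap improvement in precision. The primary comparison leaves out a covariate that the protocol itself calls prognostic and already extracts, and the factor by which it stratifies. For RCT size alone, the 95% interval would change from 0.3% wider (r = 0) to about 8% narrower (r = 0.4), with power for 11 points between about 80% and about 87%. These figures rest on the protocol's SD of 0.25 and 83 articles per arm, and on an assumed r. The documents do not support calling the planned analysis biased or the trial too small.

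**What to change.** In section 4.8.3, make the primary estimate the arm coefficient, that is the difference in mean proportion with its 95% confidence interval, from a pre-specified linear model containing arm, log(number of participants randomised in the reported RCT) and journal, with small journals grouped by a rule stated in advance. Use this model whatever the histogram shows, in place of the distribution-dependent switch to Wilcoxon-Mann-Whitney, which does not itself yield an interval for the mean difference. Keep the unadjusted t-test difference as a supporting result.

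In Table 2, define sample size as the number of participants randomised and state a convention for cluster and crossover trials. Section 4.2 admits cluster trials and Table 2 foresees crossover designs, so a raw count would not mean the same thing across articles.

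The cost is a few sentences and a definition, on a characteristic already listed for extraction. Statistically it is a few degrees of freedom, and a negligible loss of precision if the covariates prove not to be prognostic.

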## 4. Methods

### 4.1 Trial design

This study is a multicentre RCT with articles being the unit of randomisation (Figure 1; allocation ratio 1:1). A multicentre parallel arm RCT with randomisation at the individual article level was chosen instead of a cluster RCT because the risk of any “contamination” on journal level is not given as the intervention will be implemented by an external researcher (i.e. BS). The possibility of contamination due to the possibility that peer reviewer are invited to assess several RCTs and are randomised into both arms was judged as relatively small and therefore we do not plan to adjust for clustering by journal. The journal staff (i.e. editors) will not be actively told which manuscript was allocated to the proposed intervention and which to the control group.

**Figure 1:** Study flowchart

[figure not shown]

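### Randomisation is stratified by journal, but the primary comparison ignores journal for a reason that does not bear on the choice; some precision is lost, with no inflation of false positives

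*Protocol*

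**What the plan says.** Section 4.7 (Randomisation and blinding) allocates articles 1:1 "using random block sizes between 2 and 8 and stratification by journal". Journal is entered into the randomisation system for every article.

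Section 4.8.3 compares the arms with an unpaired Student's t-test "to compare the unadjusted mean proportion of adequate reporting". Its fallback is also unstratified: "If the data is not normally distributed, comparisons will be performed using a non-parametric equivalent test", named there as Wilcoxon-Mann-Whitney. Section 4.8.4 carries the same strategy over to the continuous secondary outcomes. The protocol describes no analysis that adjusts for or stratifies by journal.

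Section 4.1 gives the reason. The chance that a reviewer is invited for several trials and falls into both arms is judged small, "therefore we do not plan to adjust for clustering by journal".

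Two other sections treat journal-level features as relevant to the outcome. Section 4.6 reports that one likely participating journal has a template that should secure three of the ten items. Section 4.8.5 plans displays by whether the journal enforces CONSORT and by impact factor, and cites evidence that impact factor is associated with adherence.

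**The concern.** Stratified blocking makes the arms similar in journal mix, so differences between journals largely drop out of the treatment contrast. The t-test's pooled SD still contains those differences, so its standard error describes a less precise design than the one being run. Intervals come out too wide and p-values too large on average.

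The stated reason does not address this. Reviewers who see both arms would dilute the treatment effect. Whether a stratification factor that predicts the outcome should be in the model is a separate question, and a low contamination risk is no argument against including it.

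This does not depend on what a separate analysis plan might contain, because the protocol itself makes the choice and gives its reason. At stake is efficiency: information secured by the stratified design is not used in the analysis.

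**Working it through.** **Inputs from section 4.6.** Scenario 2, which sets the sample size: "71% adherence in control group; 82% adherence in intervention group", so a difference of 0.11; SD 0.25; 83 per arm; two-sided 5%. Scenario 1: 0.70 against 0.56, a difference of 0.14; SD 0.25; 68 per arm; 90% power.

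**Step 1. Reproduce the plan's figures (two-sample t-test, noncentral t).**
- Scenario 1: 68 per arm gives 90.0% power.
- Scenario 2: SE = 0.25 × √(2/83) = 0.0388; 0.11/0.0388 = 2.83; critical t on 164 df = 1.975; power 80.5%. The 95% CI half-width is 1.975 × 0.0388 = 0.0766.

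Both stated sample sizes hold for the unadjusted test.

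**Step 2. Share of variance due to journal (assumed).** The protocol gives no between-journal variance. As an illustration, let a proportion p of articles come from template journals whose mean differs by g from the others, with total SD 0.25:

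R² = g² × p(1 − p) / 0.25²

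I take g from 0.10 to 0.20 and p from 0.30 to 0.90. The upper end of p reflects the remark in section 4.6 that the template journal may supply a high proportion of articles. As a plausibility check on g: if the three template items were always reported at template journals, and everything else stood at the scenario 1 rates in Table 3, the means would be (441 + 300)/10 = 74.1% and (441 + 69 + 19 + 34)/10 = 56.3%. That gap is 17.8 points, inside the range.

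**Step 3. Consequences, assuming balance within journals.**
- Excess width of the unadjusted interval: 1/√(1 − R²).
- Actual type I error of the unadjusted test: 2 × [1 − Φ(1.96/√(1 − R²))].
- Power of the unadjusted test: Φ[(0.11 − 0.0766) / (0.0388 × √(1 − R²))].
- Power of the adjusted test: noncentral t with residual SD 0.25 × √(1 − R²), ignoring the degrees of freedom spent on journals.

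For g = 0.15 and p = 0.5: R² = 0.0225 × 0.25/0.0625 = 0.09. Residual SD is 0.2385, and the half-width falls from 0.0766 to 0.0731. Type I error is 2 × [1 − Φ(2.055)] = 4.0%. Unadjusted power is Φ(0.0334/0.0370) = 81.6%; adjusted power is 84.0%.

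| g | p | R² | Unadjusted CI wider by | Type I error, unadjusted | Power, unadjusted → adjusted |
|---|---|---|---|---|---|
| 0.10 | 0.90 | 1.4% | 0.7% | 4.8% | 80.7 → 81.0% |
| 0.10 | 0.50 | 4.0% | 2.1% | 4.6% | 81.0 → 82.0% |
| 0.15 | 0.90 | 3.2% | 1.7% | 4.6% | 80.9 → 81.7% |
| 0.15 | 0.50 | 9.0% | 4.8% | 4.0% | 81.6 → 84.0% |
| 0.20 | 0.90 | 5.8% | 3.0% | 4.4% | 81.2 → 82.7% |
| 0.20 | 0.50 | 16.0% | 9.1% | 3.3% | 82.6 → 86.7% |

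**Step 4. Check without the balance assumption.** Trials were simulated with blocks of 2 to 8 within 5 journals, recruitment until 83 published articles per arm, acceptance of 100% or 50%, and a journal share of variance of 9% (3,000 trials per setting). The unadjusted t-test had type I error of 4.2–4.3%, against 4.7–5.5% with journal in the model. Power was 83% against 84–85%, and the unadjusted intervals were 3–4% wider. The direction survives the loss of unpublished manuscripts; the size is slightly smaller than in the idealised formula.

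**The case against.** **The size of the journal effect is not in the protocol.** This stands. A reader might take Table 3 to say that template journals report 71% of items and other journals 56%. It does not. Its two columns are alternative trial-wide assumptions: the control-arm rates of an earlier study, and the same rates with three items set to 90% overall. The protocol supports the view that journals differ, but not by how much, and the true variance share could be near zero. Nor do the illustrative mixtures reproduce scenario 2: with 30–70% of articles at 71% and the rest at 56%, the overall mean would be 60.5–66.5%, not 71%. The gaps above serve only as assumptions about variance.

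**The trial was sized for exactly this test.** This also stands. The 83 per arm gives 80.5% power with the full SD of 0.25, itself raised from the 0.23 seen in the earlier study; at 0.23 the unadjusted power would be 86.5%. A reader might infer that the trial is underpowered, and the figures do not support that.

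**Validity is not at risk.** A reader used to cluster trials might infer that ignoring journal makes intervals too narrow. Here articles are randomised within journals, so the error runs the other way. The unadjusted difference is not biased by this choice either.

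**Balance within journals is only approximate**, because section 4.8.1 analyses accepted manuscripts only. That is correct, and it is why the type I figures in the table are idealised. It does not favour the unadjusted test: a chance imbalance in journal mix among published articles is corrected by adjustment and left in place without it.

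**Adjustment has a price.** Section 4.2 admits journals with as few as five trial reports in 2017 and gives no number of journals, so sparse strata are plausible. The remedy needs a rule for them.

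**Conclusion.** The mismatch is real: the design stratifies by journal, both branches of the primary analysis ignore it, and the reason in section 4.1 does not bear on the choice. The consequence is a modest, conservative loss of precision.

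Under assumed gaps of 10–20 points and 30–90% of articles from template journals, journal explains about 1–16% of variance. The unadjusted interval is about 1–9% wider than necessary, and type I error is about 3.3–4.8% instead of 5% if balance within journals is assumed. Adjustment adds about 0.3 to 4 points of power (81.0 − 80.7 at one end, 86.7 − 82.6 at the other). If one template journal supplies 80–90% of articles at a 15-point gap, the gain is about 1 point. If journals do not differ, there is none.

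The stated 80% power is met either way, and the omission does not raise the false-positive rate. The case for the change is that it is nearly free, not that the planned analysis is invalid.

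**What to change.** - **Primary analysis (4.8.3):** a linear model of the article's proportion score on arm and journal, with either a random intercept for journal or fixed effects with sparse journals pooled by a rule set in advance. Report the adjusted mean difference with its 95% CI. Keep the unadjusted t-test as supportive.
- **Rank-test branch (4.8.3):** if a rank test is used, make it journal-stratified (van Elteren).
- **Secondary outcomes (4.8.4):** adjust for journal with a method suited to each outcome type, for example Mantel-Haenszel risk differences for rejection, publication and single items.
- **Trial design (4.1):** remove low contamination as the reason for not adjusting by journal.

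The sample size need not change, and journal is already recorded at randomisation. The cost is protocol wording and a few degrees of freedom, more if many small journals take part. Settle it before outcome data are seen, since a covariate added later would look data-driven.
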